### Patients

All patients who are over 65 years old, diagnosed with HTN and/or hypercholesterolemia, and included in a program for following-up chronic patients in PHCCs will be included. The patient must be under treatment with at least one of the following drugs: enalapril, amlodipine, and simvastatin, with a stable dose during the previous 3 months, and must give informed, written consent.

The criteria for exclusion are: having difficulty to properly understand written or spoken Spanish, foreseeing an address change and not being ascribed to the PHCC for the following year, and suffering from severe systemic disease or other limitations that prevent the patient from attending the PHCC for the follow-up visits.

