### Sample size

Sample size has been calculated to estimate a proportions difference in the degree of adherence to the treatment of 20% between the exposed group (drug changes at the pharmacy) and the non-exposed group. It is estimated that adherence to treatments in the population undergoing chronic treatment is 50%, and the odds ratio (OR) of suffering an event of adherence decrease is double in the group exposed to drug changes (OR = 2) versus the non-exposed one.

For an alpha error of 0.05 and a beta error of 0.20, 237 patients would be necessary. Taking into account the effect of the doctor on adherence of their patients to treatment, it is considered that the outcome of each patient is not independent from other patients from the same cluster, so it is necessary to adjust the sample size because of the design effect. Considering that the number of included patients per doctor is 15, and assuming an intraclass correlation coefficient of 0.01 [17], the required sample size would be 240. If we estimate a 7% loss of patients to follow-up within a one-year period, the final sample size will be 259 patients.

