### Variables

The main outcome variable is a final combined variable, defined as “having made some drug usage error and/or an inadequate adherence to treatment regimen”.

Error in drug usage is defined according to the classification proposed by Ruiz-Jarabo *et al*. [18]. The type of error will be recorded (wrong dose, wrong frequency), as well as if there was injury to the patient, in which case the type and severity will also be recorded.

Inadequate adherence will be considered if more than one forgotten dose is detected during the package counting and/or if any of the answers (Yes/No) to the 4 questions of the Morisky-Green test in its validated Spanish version [19] is wrong. In the case of discrepancies between the Morisky test and the counting, the outcome of the counting will prevail. Since one single forgotten dose is a very stringent level of accomplishment, if no adherence differences are observed, different degrees of adherence (80%, 90% and 110%) will be considered.

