### Secondary outcome variables

#### Sociodemographic

Age, sex, level of education (illiterate, without studies, primary studies, secondary studies, superior education), and PHCC.

Related to the prescription and active ingredient:Prescribed active ingredient: enalapril, amlodipine, or simvastatin.Change of drug presentation at the pharmacy (Yes/No).Number of changes per drug.Suffering an adverse reaction to the drug (Yes/No), interruption of medication (Yes/No), and the reason for such interruption.Number of avoidable and non-avoidable adverse effects during the follow-up period.Tolerance of the patients to the dispensed drugs according to their own direct statement.

Clinical and analytical:Years of development of HTN and/or dyslipidemia. Presence of pathologies that modify the HTN (nephropathologies, sleep apnea, obesity, and malnutrition). Presence of pathologies that modify the lipid profile (hyperthyroidism, hypothyroidism, obesity, and malnutrition). Comorbidity (cardiovascular pathology, neurological pathology).Treatments that modify BP and the lipid profile (diuretics, alpha and beta blockers), anti-inflammatories, antidepressants and anxiolytics, thyroxin, hormone replacement therapy. Other concomitant treatments.Figures of systolic blood pressure (SBP) and diastolic blood pressure (DBP) in each visit. Difference of SBP and DBP between the first visit and the last recorded data. Percentage of patients with good control at the beginning and at the end of the study.Total HDL cholesterol, LDL cholesterol, and triglycerides, both initial and after one year.Initial and final weight. Initial height. Difference in body mass index (BMI) between the first and final visits.

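### The unscaled limit on forgotten doses and the any-change exposure both rise with the number of study drugs, and the plan does not guarantee adjustment for that number

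*Protocol article*

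**What the plan says.** All references are to the protocol article.

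- **Patients:** treatment with "at least one of the following drugs: enalapril, amlodipine, and simvastatin" is required, so a participant may take one, two or three study drugs.
- **Variables:** the main outcome is one composite per patient (usage error, inadequate adherence, or both). Adherence is inadequate if "more than one forgotten dose is detected during the package counting" or if a Morisky-Green answer is wrong. Where the two disagree, the count decides. Percentage degrees of adherence (80%, 90%, 110%) come in only if the strict limit shows no difference.
- **Secondary outcome variables:** the list includes the prescribed active ingredient, the item "Change of drug presentation at the pharmacy (Yes/No"), and the number of changes for each drug. The number of study drugs is not an item of its own.
- **Sample size:** the unit is the patient. An exposed group is compared with a non-exposed group, and the odds of an adherence event are taken as "double in the group exposed to drug changes (OR = 2) versus the non-exposed one".
- **Data analysis:** proportions are compared by chi-square or Fisher's test. A logistic model then takes the variables that were associated with the outcome in the bivariate step. No covariate is named as always included.

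**The concern.** The limit is the same absolute number for every patient. At one dose per drug per day (an assumption), a 90-day interval holds 90, 180 or 270 scheduled doses for one, two or three drugs. The patient on three drugs has three times as many opportunities to exceed the limit, and also three products whose presentation can change. Patients on more drugs would thus gather in the exposed group and among the cases even if a change of appearance did nothing.

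At stake is the reading of the main association. The bias favours the study hypothesis. The percentage degrees of adherence, which carry a denominator, are consulted only after a null result, so a spurious difference would leave that check unused.

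**Working it through.** **Plan's own yardstick.** With "adherence to treatments in the population undergoing chronic treatment is 50"%, the odds are 1. Doubling them gives 2/(1 + 2) = 66.7%. The calculations below use the 240 patients required before losses (240/0.93 = 258.1, hence the stated 259). How the plan arrives at 240 does not affect this point.

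**Assumptions, not in the article.** The mix of patients on k = 1, 2, 3 drugs; the chance c that a given drug changes presentation during the year; missed doses per drug with mean λ; and no effect of changes on adherence. Given k, outcome and exposure are independent.

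**Formulas.** Exposure: 1 − (1 − c)^k. Outcome, if missed doses are summed over drugs: 1 − exp(−kλ)(1 + kλ). Here λ is chosen so that about half of all patients have the outcome, in line with the plan's 50%.

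**Main case: mix 60/30/10%, c = 0.5, λ = 1.21.**

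| k | share | exposed | outcome |
|---|---|---|---|
| 1 | 0.60 | 50.0% | 34.1% |
| 2 | 0.30 | 75.0% | 69.6% |
| 3 | 0.10 | 87.5% | 87.7% |

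- Exposed: 0.300 + 0.225 + 0.0875 = 0.6125 of patients.
- Outcome if exposed: (0.300×0.341 + 0.225×0.696 + 0.0875×0.877)/0.6125 = 54.8%.
- Outcome if not exposed: (0.300×0.341 + 0.075×0.696 + 0.0125×0.877)/0.3875 = 42.7%.
- Crude odds ratio: (0.548/0.452)/(0.427/0.573) = 1.63, with no true effect. At 240 patients, a two-sided 5% test would reject in about 45% of studies.

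**A second model.** Mix 50/35/15%, a 1% miss probability per dose over 90 days (binomial) and c = 0.4 give outcomes of 22.7%, 53.8% and 75.3% and exposures of 40%, 64% and 78.4% for k = 1, 2, 3. The crude odds ratio is 1.65 (47.0% against 35.0%).

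**If the limit must be exceeded on a single drug.** In the second model the outcomes become 1 − (1 − 0.227)^k = 22.7%, 40.3% and 53.9%, and the odds ratio is 1.37 (36.8% against 29.8%). The confounding shrinks but stays.

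**Range.** Three mixes were used (40/40/20, 60/30/10, 80/17/3), with c from 0.2 to 0.7, with and without gamma variation in miss rates between patients:

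- Highest: mix 40/40/20, c = 0.7, no variation, odds ratio 2.06.
- Lowest: mix 80/17/3, c = 0.2, strong variation (shape 0.5), odds ratio 1.10.
- False-positive rates run from about 5% to 55%.

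**Adjusted models.** These come from 3,000 simulated studies of 240 patients per setting, in six settings, all with c = 0.5 and no true effect.

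| model | median odds ratio | false positives |
|---|---|---|
| crude | 1.32–1.79 | 19–55% |
| ingredient indicators kept if p < 0.05 | 1.07–1.21 | 6–10.5% |
| all three ingredient indicators forced in | 1.01–1.02 | 4.5–5.8% |
| number of study drugs forced in | 1.00 | 4.3–5.6% |

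If every patient takes one drug, the crude odds ratio is 1.00 with about 5% false positives. This confirms that the number of drugs is the source.

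**The case against.** A reader might infer that the plan adds up missed doses and changes over all study drugs, and that a false association must then appear. The article does not support either step. It never states that doses are summed, and it records the number of changes for each drug. What it leaves open is the unit of the count and of the yes/no exposure. This corrects the reading without removing the problem, because an outcome per patient with an unscaled limit is affected under both counting rules.

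The strongest defence is the planned model. Active ingredient is a listed variable, and three separate indicators determine the number of study drugs exactly. If that number drives the outcome strongly, the indicators will often pass the screen, and most of the bias goes. This stands, with three limits:

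- Nothing ensures that the indicators pass.
- The coding is not stated, and one three-level variable cannot describe a patient on two drugs.
- The crude difference and its test remain unadjusted.

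The size also rests on assumptions. With mostly one-drug patients and strong variation in miss rates, the bias is small. The calculation treats the dose count as the whole outcome and does not model usage errors, the questionnaire or clustering by doctor.

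Finally, the article itself recognises that its limit is strict and names percentage degrees of adherence. Because these apply only after a null result, they do not protect against a spurious positive one.

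**Conclusion.** The point holds as a risk of confounding, not as a certain false finding. The number of study drugs raises both the outcome and the exposure as the article defines them, and the crude comparison is biased towards the hypothesis. The null crude odds ratio is about 1.1 to 2.1 under the assumed mixes, change rates and miss-rate variation, so the upper end reaches the planned odds ratio of 2. The multivariable result may be close to unbiased (about 1.07 to 1.21 after the screen in the settings simulated), but the plan does not secure this. It is a cheap improvement worth making before analysis, not a flaw that invalidates the design.

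**What to change.** 1. Make doses taken divided by doses scheduled the primary definition of count adherence, with one percentage limit set in advance and not conditional on a null result. State the counting interval and whether the ratio is pooled over a patient's study drugs or judged drug by drug.
2. State whether the yes/no exposure is per patient or per drug.
3. Force the number of study drugs (1, 2, 3) into the primary model whatever its bivariate result. Scaling alone is not enough: the chance of crossing a percentage limit can still depend on the number of drugs, for instance if failing on any one drug counts.
4. Optionally, analyse patient-drug records, pairing each drug's adherence with changes of that same drug, clustered in patient and doctor.

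The cost of items 1 to 3 is rewording the outcome and exposure and adding one or two model terms. Packages are already counted, and active ingredient and changes per drug are already recorded. Item 4 needs one more level of clustering.

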### Data analysis

Data will be reviewed prior to analysis to guarantee its quality. A descriptive analysis will be performed on the characteristics (age and sex) of patients who refuse to participate in the study and the reasons for it will be described.

A descriptive analysis of each of the variables will be carried out. The mean and typical deviation will be calculated in the case of symmetric distributions, and median and interquartile ranges will be estimated if the distribution is asymmetric. For categorical data, the frequency and percentage distributions will be shown. The difference of proportions will be estimated with its relevant confidence interval of 95%.

The association of each of the independent variables with the dependent variable (adherence decrease and medication errors) will be studied, using Pearson’s Chi-square test or Fisher’s exact test (when the conditions to apply Chi-square are not satisfied) as the statistical tools to compare proportions, and the Student’s T distribution or the Mann–Whitney U non-parametric test to compare the means.

A multivariate test with a logistic regression model will be performed, using the final combined variable (adherence and medication errors) as the dependent variable, and using as independent variables those identified to be associated in the bivariate analysis. All the hypothesis testing will be performed for all analysis’, and a p < 0.05 will be accepted as significant. All the analysis methods will be adjusted considering cluster randomizations [20]. Statistical data analysis will be performed using SPSS 18.0 software.

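### The adherence cut-off moves to 80%, 90% or 110% only after a null result, so the false-positive rate of the main adherence claim exceeds the stated 5%

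*Protocol article*

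**What the plan says.** All references are to the Protocol article, Methods/design.

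- **Main outcome (Variables).** "The main outcome variable is a final combined variable", made up of a drug usage error and/or inadequate adherence.
- **Adherence component (Variables).** "Inadequate adherence will be considered if more than one forgotten dose is detected during the package counting", and/or if any Morisky-Green answer is wrong. Where the two disagree, the count decides.
- **Conditional clause (Variables).** Having called this level very stringent, the text continues: "if no adherence differences are observed, different degrees of adherence (80%, 90% and 110%) will be considered".
- **Testing (Data analysis).** For all hypothesis tests, "a p < 0.05 will be accepted as significant". Nothing adjusts for the extra cut-offs, labels them as sensitivity or exploratory analyses, or says which one decides the conclusion.
- **Design error rates (Sample size).** "For an alpha error of 0.05 and a beta error of 0.20, 237 patients would be necessary". The calculation is built on a difference in adherence between exposed and non-exposed patients.

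**The concern.** The definition of adherence depends on the result it produces. If the first cut-off separates the exposure groups, it stands. If it does not, up to three others may be tried on the same patients, each at 0.05. The rule runs one way only: it can turn a null into a positive, never the reverse.

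Adherence is the quantity the study is sized on and half of its main aim, so the stated alpha of 0.05 no longer describes the chance of a false claim on the main question. The fallback is also a realistic path, because the authors themselves expect the first level may be too strict to discriminate. A positive result from a later cut-off would carry a nominal p below 0.05 that overstates the evidence, in a study whose Discussion hopes to shed light on how recent legislation affects patient safety.

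**Working it through.** **Inputs from the article**
- Level per test: 0.05, with no adjustment (Data analysis).
- Definitions that may be tested: one first cut-off plus three fallbacks, k = 4 (Variables). If 110% is not a separate attempt, k = 3.
- Analysable patients: 259 × (1 − 0.07) = 240.9, so 240 or 241 (Sample size).

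**Assumed, because the article does not give them**
- The distribution of percent adherence.
- A 1:1 split of exposed and non-exposed patients.
- About 365 scheduled doses in the year.
- The frequency of usage errors.

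**Step 1. The plan's own figure.** One fixed definition tested once at 0.05 has a type I error of 0.05. Simulation reproduces this: 0.049 in the first set below.

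**Step 2. Bounds that need no distribution.** With tests of exact level 0.05, 0.05 ≤ P(at least one p < 0.05) ≤ k × 0.05 = 4 × 0.05 = 0.20. The lower bound is reached only if a later cut-off never rejects when the first has not.

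**Step 3. Independent tests.** P = 1 − (1 − 0.05)^k.

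| k | P(at least one false positive) |
|---|---|
| 1 | 0.050 |
| 2 | 0.0975 |
| 3 | 0.143 |
| 4 | 0.185 |

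**Step 4. Correlated cut-offs, simulated under no effect.** The same patients are classified by each cut-off, and each is tested with the pooled z statistic, z = (p₁ − p₂) / √[p(1 − p)(1/n₁ + 1/n₂)], rejecting if |z| > 1.96.

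| Assumed data | All four cut-offs | Three missed-dose cut-offs | One fixed definition |
|---|---|---|---|
| Negative-binomial missed doses (mean 25/365) and extra doses (mean 12/365), 241 patients, 20,000 runs | 17.6% | 13.2% | 4.9% |
| Normal percent adherence, mean 0.90–1.00, SD 0.10–0.15, 120 vs 120, 40,000 runs; 110% as a separate cut-off or as the upper end of an 80–110% band | 14.5–17.3% | not run | 4.3–5.4% |
| Negative-binomial doses with usage errors in 0–50% of patients added to every version of the outcome, 120 vs 120, 20,000 runs | 12.7–18.7% | 11.0–14.0% | 3.7–5.2% |

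In the third setting, reading 110% as the upper end of a band gave 12.5–17.1%. A separate run of the same kind with three dispersions gave about 12–18% for four cut-offs and 10–14% for three.

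The first row implies that 81% of patients miss more than one dose, 20% fall below 90% adherence, 6% fall below 80% and 7% exceed 110%. The Sample size section plans on 50% adherence. The normal case with mean 1.00 and SD 0.10 puts 48.4% of patients over one missed dose, close to that figure, and gives 16.6% or 16.5% under the two readings of 110%. The inflation therefore does not depend on the 81%.

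**Step 5. What the fallback contributes.** From the first row, 0.176 − 0.049 = 0.127 of null studies become positive only through a later cut-off. That is 0.127 / 0.176 = 72% of all false positives, and 0.127 / (1 − 0.049) = 13% of null studies whose first test was correctly negative.

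These rates are computed under no effect and do not rest on how the 237 or 259 patients were derived.

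**The case against.** The strongest case is about scope and size.

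- **Scope.** The clause speaks of adherence differences, one component of a composite, and says only that other levels will be considered. It does not state that the composite is recoded or that a later cut-off decides. This stands as a limit on wording. It does not rescue the rule: the clause sits inside the definition of the main outcome, nothing labels it secondary, and on the narrower reading the same inflation attaches to the adherence claim on which the study is sized.
- **Shared usage errors.** Errors counted in every version make the tests more alike and lower the rate. This stands, and it puts 17.6% towards the upper end. With usage errors in half of the patients, one four-cut-off run gave 13.5%, still well over twice nominal.
- **Meaning of 110%.** It may be an upper limit, not a fourth attempt. This is fair, and both readings were run. Band readings gave roughly 12–17%.
- **Direction.** The hypothesis is one of harm, and the rates above count errors both ways. A false finding of harm occurred in about 7–9% of runs with four cut-offs, against about 2.5% with one definition. The absolute figure is smaller, but the inflation is about threefold.
- **Transparency.** The list is short and published in advance, so a reader can discount a late positive. That softens the consequence, but only if the report says which cut-offs were tried and in what order, which the article does not require.
- **A separate analysis plan might add control.** The point is not an omission. The article itself states a result-triggered rule.

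**Conclusion.** The concern holds. As written, the type I error of the adherence claim is above 0.05 and at most 0.20, whatever the data look like, unless the later cut-offs never reject when the first does not. Under the assumed distributions it is about 12–19% with four cut-offs and 10–14% with three, against about 5% for one fixed definition. The exact figure depends on the adherence distribution, the frequency of usage errors, the exposure split and the reading of 110%, none of which the article fixes. The simulations also use simple two-group tests, without the logistic model or clustering by doctor. The direction of the error depends on none of these. It should be put right before data are seen, since a choice of cut-off made afterwards cannot be shown to be independent of the result.

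**What to change.** In Variables, name one adherence cut-off for the main outcome before data are seen and delete the conditional clause. If the authors already think more than one forgotten dose is too strict, they should replace it now; a count-based 80–110% band is one example, and the choice is theirs. State whether 110% is an upper limit or a separate cut-off. Add that results at the remaining cut-offs will be reported whatever the primary result, as sensitivity analyses that cannot replace it. The adherence claim then has its 5% error rate back.

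If the authors want all four cut-offs to be able to support the claim, the tests need adjustment; Bonferroni gives 0.05 / 4 = 0.0125 each, at some loss of power.

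The main option costs a sentence or two of text, with no extra patients, visits or data.

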### Secondary outcome variables

#### Sociodemographic

Age, sex, level of education (illiterate, without studies, primary studies, secondary studies, superior education), and PHCC.

Related to the prescription and active ingredient:Prescribed active ingredient: enalapril, amlodipine, or simvastatin.Change of drug presentation at the pharmacy (Yes/No).Number of changes per drug.Suffering an adverse reaction to the drug (Yes/No), interruption of medication (Yes/No), and the reason for such interruption.Number of avoidable and non-avoidable adverse effects during the follow-up period.Tolerance of the patients to the dispensed drugs according to their own direct statement.

Clinical and analytical:Years of development of HTN and/or dyslipidemia. Presence of pathologies that modify the HTN (nephropathologies, sleep apnea, obesity, and malnutrition). Presence of pathologies that modify the lipid profile (hyperthyroidism, hypothyroidism, obesity, and malnutrition). Comorbidity (cardiovascular pathology, neurological pathology).Treatments that modify BP and the lipid profile (diuretics, alpha and beta blockers), anti-inflammatories, antidepressants and anxiolytics, thyroxin, hormone replacement therapy. Other concomitant treatments.Figures of systolic blood pressure (SBP) and diastolic blood pressure (DBP) in each visit. Difference of SBP and DBP between the first visit and the last recorded data. Percentage of patients with good control at the beginning and at the end of the study.Total HDL cholesterol, LDL cholesterol, and triglycerides, both initial and after one year.Initial and final weight. Initial height. Difference in body mass index (BMI) between the first and final visits.

